#### Crash data

Police-reported crash data will be accessed through each of the three states’ respective Department of Transportation and will be used to assess the trial’s primary hypothesis. Participants’ licence numbers (collected in the pre-trial questionnaire) will be used to access police-reported crash data. Crash data obtained will include not only binary data, i.e., ‘yes/no’ data on whether a driver was involved in a crash, but also the number of crashes (if the driver was involved in more than one). Data will be obtained for all drivers – both the intervention and control groups – blind to group status.

#### Confidentiality

The survey data gathered through Qualtrics will be exported and stored in MediaFlux and OneDrive, both managed by the University of Melbourne and accessible only to authorised trial staff. Before storing the data, a unique identifier will be generated for each participant, and survey responses that cannot be linked to specific individuals will be stored in MediaFlux and OneDrive. Sensitive and identifiable information such as driver’s license numbers, mobile numbers, and email addresses will be encrypted and stored in MediaFlux. Personal data will be destroyed after each participant’s 28-week trial period. Participants’ driver’s licence numbers will only be shared with their respective state’s Department of Transportation to access information on crash events.

The mobile telematics data collected via the smartphone app will be stored in an AWS S3 bucket and Microsoft SQL Server managed by UA, which has appropriate security measures and privacy in-place for the data stored in their servers. Any survey responses, including demographic details and responses to driver behaviour questions, may be shared in research publications but will not include identifiable information.

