### Study timeline

Each participant will be involved in the trial for a total of 28 weeks, consisting of a 4-week baseline period, 20-week post-randomisation (intervention) period, and 4-week post-intervention period. To join the trial, a participant will sign a consent form and complete a pre-trial questionnaire. Upon consent and completion of the pre-trail questionnaire participants will receive a link via SMS to download the FEEDBACK app. Once a participant downloads the FEEDBACK app and pairs the smartphone with their car (via Bluetooth), their participation in the trial will commence.

During the 4-week baseline period, the FEEDBACK app will collect data on the participant’s driving behaviours: speeding, braking, and acceleration. However, the app will not display any information to the participants during the baseline period (see Fig. 1a). After the 4-week baseline, participants will be randomised (as discussed in Sect. 2.6) into either the control group or intervention group for the next 20-week intervention period.

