At the end of this post-intervention period, participants will receive a link to the post-trial questionnaire. Upon completing the questionnaire, the control group will be entered into one final draw. The intervention group will be able to receive the remaining funds of their safe driving accounts via an e-voucher. Figure 2 illustrates an overview of the aforementioned activities conducted during each stage of the trial timeline.

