### Hypotheses and outcome measures

The **primary hypothesis** will assess whether personalised safety feedback and personalised financial incentives reduce the incidence of police-reported crashes of any type during the 24-week intervention and post-intervention periods. The primary outcome is a police-reported crash over the 24-week intervention and post-intervention periods. The research team will obtain data on police-reported crashes using drivers’ licence numbers provided by participants in the pre-trial questionnaire.

The **secondary hypotheses** will assess the effects of personalised feedback and financial incentives on:

Reducing the incidence of self-reported crashes by young drivers.Improving drivers’ safety scores (‘DrivePoints’ scores) from baseline.Reducing crash risk behaviours identified by speeding, harsh braking, hard acceleration, and drowsy driving from baseline.

The **outcomes** to assess the secondary hypotheses are:

Self-reported involvement in a crash that took place during the 24-week intervention and post-intervention periods that resulted in damage to their own or someone else’s vehicle.DrivePoints score at baseline and at weekly intervals through to week 28.Driving behaviours, namely:
Speeding (defined as 10 km/h over the speed limit).Harsh braking (sudden braking in which items in the vehicle would move around, defined in telematics technology as a -0.5 g force).Hard acceleration (rapid acceleration exceeding a 0.25 g force).

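### Destruction of licence numbers is triggered by each participant's week 28, when the primary outcome window closes, with no exception for completing the crash linkage

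*Protocol article*

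**What the plan says.** Four parts of the protocol article bear on this.

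- **Outcome and window.** Hypotheses and outcome measures: "The primary outcome is a police-reported crash over the 24-week intervention and post-intervention periods". Study timeline describes participation as "consisting of a 4-week baseline period, 20-week post-randomisation (intervention) period, and 4-week post-intervention period".
- **Linkage key.** Crash data: "Participants’ licence numbers (collected in the pre-trial questionnaire) will be used to access police-reported crash data". Hypotheses and outcome measures repeats this: "The research team will obtain data on police-reported crashes using drivers’ licence numbers provided by participants in the pre-trial questionnaire". No other key is named.
- **Retention.** Confidentiality first lists what is identifiable: "Sensitive and identifiable information such as driver’s license numbers, mobile numbers, and email addresses will be encrypted and stored in MediaFlux". The next sentence is the destruction rule: "Personal data will be destroyed after each participant’s 28-week trial period". The sentence after that returns to licence numbers: "Participants’ driver’s licence numbers will only be shared with their respective state’s Department of Transportation to access information on crash events".
- **Steps at or after week 28.** Personalised financial incentives: "At the end of this post-intervention period, participants will receive a link to the post-trial questionnaire". The control group's final draw and the intervention group's e-voucher follow completion of that questionnaire.

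The article gives no date for the crash request, no retention interval and no exception for linkage.

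**The concern.** The event that ends the outcome window also triggers destruction of the key to that outcome. An extract taken before week 28 ends cannot cover the full window. An extract taken afterwards needs an identifier that, under the stated rule, is due for destruction. Crashes late in the window may also take time to reach the state record, although the article gives no such lag.

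Because the trigger is each participant's own week 28, it does not wait for the last participant, for all three states, or for a checked data set. If the rule were applied promptly:

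- late-recorded crashes could not be picked up by a second request;
- a faulty extract could not be corrected;
- one pooled request at the end of follow-up would come too late for early participants, who would then have no primary outcome.

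A destroyed key cannot be rebuilt from anything else the article describes. The same sentence also covers the contact details used for the questionnaire, which supplies the self-reported crash outcome, and probably those used for the vouchers.

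**Working it through.** **1. Timeline.** From Study timeline, participation lasts 4 + 20 + 4 = 28 weeks. The outcome window is 20 + 4 = 24 weeks and follows the 4-week baseline, so it covers trial weeks 5 to 28. Its last day is the last day of the 28-week period named in the destruction rule.

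**2. Does the rule cover licence numbers?** Confidentiality does not define personal data. The preceding sentence gives licence numbers as the first example of identifiable information, and the following sentence restricts how they are shared. Read in sequence, the rule includes them.

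**3. Reproducing the sample size.** Inputs from Sample size: 3% v 1.5%, two-sided 5%, power 80%; 1:1 allocation from Randomisation and blinding. With the pooled two-proportion formula and no continuity correction:

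n = [1.960 × √(2 × 0.0225 × 0.9775) + 0.8416 × √(0.03 × 0.97 + 0.015 × 0.985)]² / 0.015²

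= (0.4111 + 0.1763)² / 0.000225, which rounds up to 1,534 per arm, or 3,068 in total. Then 1,534 / 0.85 rounds up to 1,805 per arm, or 3,610. Both match the article. Planned events at 1,534 per arm are 1,534 × (0.03 + 0.015) = 69.

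**4. Sensitivity to missed crashes.** The lag is an assumption. Suppose crashes are spread evenly over the 24 weeks and those in the last L weeks are missed in the same proportion in both arms. The share missed is L/24, and each arm's risk is multiplied by (1 − L/24). Then

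power = Φ{ [(p₁ − p₂)√n − 1.960 × √(2p̄(1 − p̄))] / √(p₁(1 − p₁) + p₂(1 − p₂)) }.

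For L = 4 and n = 1,534, the risks are 2.5% and 1.25%: (0.4896 − 0.3760) / 0.1916 = 0.593, so power is 72.3%.

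| Last weeks missed | Share missed | Events missed of 69 | Observed risks | Power, 1,534 per arm | Power, 1,805 per arm |
|---|---|---|---|---|---|
| 0 | 0% | 0 | 3.0% v 1.5% | 80.0% | 86.0% |
| 1 | 4.2% | 3 | 2.88% v 1.44% | 78.3% | 84.5% |
| 2 | 8.3% | 6 | 2.75% v 1.38% | 76.4% | 82.8% |
| 4 | 16.7% | 12 | 2.5% v 1.25% | 72.3% | 79.1% |
| 8 | 33.3% | 23 | 2.0% v 1.0% | 62.5% | 69.6% |

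The ratio of observed risks stays at 0.5 in every row, because both arms lose the same share. The absolute difference shrinks from 1.5 to 1.0 percentage points at L = 8.

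**5. Effect of the fix on the sample size.** None: 3,068 and 3,610 stand.

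**The case against.** The strongest reply is that the rule says after the 28 weeks, with no deadline. A request sent after week 28 and before destruction complies with it. The plan's own steps also suggest that same-day deletion was not meant, since the questionnaire link, the final draw and the vouchers fall at or after week 28 and need some means of contact. The sentence following the rule provides for sending licence numbers to the state departments, and destroying the trial's copy need not stop a department from reporting on a list it already holds. Finally, a journal article need not set out the linkage workflow or extract dates.

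Much of this stands, and it rules out several stronger readings that a reader might infer:

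- *That complete linkage is impossible.* This needs immediate destruction, or a recording lag that outlasts retention. Neither is stated.
- *That a driver who was never linked would be counted as crash-free.* The article does not say so. Crash data expects a yes/no answer for every driver, a driver never submitted would have a missing outcome, and the primary analysis section plans multiple imputation as a sensitivity analysis.
- *That losses would concentrate in the slowest state.* Nothing in the article supports this, and randomisation is stratified by state.
- *That power would be lowest at the 1,534 figure.* The 15% allowance covers withdrawal, phones turned off and app deletion. The last two need not remove a crash outcome taken from state records, so the 1,805 column may be closer.

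One part of the reply does not hold. The missing workflow is not the point. The article does state a retention rule, and its trigger is the wrong event for protecting the primary outcome. If prompt deletion was not intended, the sentence still needs correcting.

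**Conclusion.** The point holds as a risk to ascertainment of the primary outcome, not as proof that the outcome will be lost. The article ties destruction of the only named linkage key to the moment the outcome window closes, separately for each participant and with no exception for linkage. Nothing in it prevents prompt application, and the result would be irreversible.

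The size cannot be fixed from the document. For 1 to 8 missed weeks, power would be 78.3% to 62.5% at 1,534 per arm (80.0% planned), or 84.5% to 69.6% at 1,805 per arm (86.0% with full ascertainment). This assumes evenly spread crashes, equal proportional loss in both arms, and no later extract to recover what was missed. Under the same assumptions absolute risks are understated and the risk ratio is roughly unchanged, so the harm is to power and absolute effect, not to the direction of the estimate. Participants whose key was destroyed before any request would have no primary outcome at all. The sample size calculation itself is correct.

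**What to change.** Replace the destruction sentence in Confidentiality with a rule tied to completion of linkage:

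- Keep licence number and study ID, encrypted, in a separate linkage file until the final crash extract from all three states, covering every participant's full 24 weeks, has been received and checked.
- Keep contact details until the post-trial questionnaire is closed and vouchers are issued.
- Then destroy both.

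It would help to state when the final extract is requested. Check that the ethics approvals and the consent wording agree with the new rule; the consent pages are not available here, so whether they need changing cannot be judged.

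The cost is longer storage of identifiers, which is a real privacy cost, and possibly a short ethics amendment. No extra participants or procedures are needed.

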### Statistical analysis

A formal detailed statistical analysis plan will be written by the trial biostatistician and published on our research centre’s website while blind to group allocation. The analysis will include all participants according to their randomised allocation.

#### Primary outcome

The primary outcome, whether a young driver had a police-reported crash of any type during the 24-week intervention and post-intervention periods, will be analysed using a log-binomial regression model. Should the log-binomial regression model fail to converge, a Poisson regression model with robust standard errors will be used. The primary hypothesis will be evaluated by obtaining the estimated relative change in the risk of a young driver being involved in a police-reported crash of any type (i.e., risk ratio) for participants in the intervention group compared to the control group, a two-sided 95% confidence interval and a p-value. This model provides valid inference in the presence of missing data if the data are missing completely at random (MCAR). A sensitivity analysis will be conducted using multiple imputation to explore the impact of any deviations from MCAR on the results.

#### Secondary outcomes

The DrivePoints score will be analysed using a constrained longitudinal data analysis (cLDA) model [42]. The response will consist of all DrivePoints scores (scores at baseline, at weekly intervals until 24 weeks post-randomisation) and the model will include factors representing treatment, time (categorical), and treatment-by-time interaction, with the restriction of a common baseline mean across treatment groups.

The total number of police-reported crashes of any type during the 24-week intervention and post-intervention periods will be analysed using a Poisson regression model. Whether a driver has a self-reported crash during the 24-week intervention and post-intervention periods will be analysed using a log-binomial regression model. Driving behaviours (i.e., binary outcomes – speeding, harsh braking, and harsh acceleration at baseline and at weekly intervals from week 4 to week 28) will be analysed using mixed-effects Poisson regression models with robust standard errors. All analysis models will be adjusted for stratification factors, study site and sex.

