### Sample size

Statistics from QLD and NSW in Australia in 2022 suggest there is a large population of P1 licence holders aged 18–20 years to sample from: 32,151 young drivers in QLD [38] and 42,039 in NSW [39]. Based on crash statistics for QLD from 2016 to 2022, the incidence of a young P1 licence holder having a police-reported crash of any type during a 6-month period is approximately 3% [40], with similar patterns expected across NSW and WA. Based on the findings of recent research [7, 8] the FEEDBACK trial intervention is expected to lower the proportion of a police-reported crashes from 3 to 1.5%.

To detect a 1.5% absolute reduction in the incidence of young drivers having a police-reported crash of any type during the 24-week intervention and post-intervention periods, from 3% in the control group to 1.5% in the intervention group (or 0.5 relative risk), using a two-sided type I error of 5% and a power of 80%, a total of 3,068 participants are required. Allowing for a 15% non-response rate due to drivers who may choose to withdraw from the study, turn off their phones, or delete the smartphone app, 1,805 participants per arm, or a total of 3,610 participants, will be recruited to participate in the trial.

To achieve adequate participant enrolment and reach the target sample size, recruitment strategies will be carried out in partnership with government stakeholders. The transport departments from the three states of Western Australia, Queensland, and New South Wales will assist with advertising the trial via several media channels, including social media, associated websites, and advertising boards in licencing centres.

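### The Poisson model for the total number of police-reported crashes names no allowance for over-dispersion; stating robust standard errors is a free, minor improvement

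*Protocol article*

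**What the plan says.** Under Secondary outcomes, the protocol article fixes the model for the crash count: "The total number of police-reported crashes of any type during the 24-week intervention and post-intervention periods will be analysed using a Poisson regression model". It names no type of standard error, dispersion term or alternative model. The covariates for every model are given in the same section: "All analysis models will be adjusted for stratification factors, study site and sex".

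Repeat crashes do enter this outcome. Under Crash data, the article says that the data will hold a yes/no indicator "but also the number of crashes (if the driver was involved in more than one)".

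Robust errors are named for two other Poisson models. One is the fallback for the primary outcome: "Should the log-binomial regression model fail to converge, a Poisson regression model with robust standard errors will be used". The other covers weekly speeding, harsh braking and harsh acceleration, which "will be analysed using mixed-effects Poisson regression models with robust standard errors". The article labels the latter outcomes as binary.

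The section on statistical analysis leaves detail to a separate analysis plan, which is not shown.

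**The concern.** Model-based Poisson standard errors assume that, given the covariates, the variance of the count equals its mean. State and sex are the only covariates. Any other lasting difference between drivers in crash risk, such as how much or where they drive, goes into the residual variation and pushes the variance above the mean. The model-based interval for the rate ratio is then too narrow and its p-value too small. This is the only stated analysis of police-reported crashes that uses repeat crashes, and so the only one in which such clustering can act in this way.

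**Working it through.** **Reproducing the plan's own figure.** The sample size is for the yes/no primary outcome: "from 3% in the control group to 1.5% in the intervention group (or 0.5 relative risk)" and "using a two-sided type I error of 5% and a power of 80%, a total of 3,068 participants are required". Pooled-variance formula for two proportions, with mean proportion 0.0225:

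n per arm = [1.960 × √(2 × 0.0225 × 0.9775) + 0.8416 × √(0.03 × 0.97 + 0.015 × 0.985)]² / 0.015² = (0.4111 + 0.1763)² / 0.000225, which rounds up to 1,534.

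The total is 3,068, as stated. Allowing for 15% loss, 1,534 / 0.85 gives 1,805 per arm and 3,610 in all, also as stated. The article gives no figure for the count analysis.

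**Inputs for the count.** From the article: the 3% and 1.5% risks, and 1,534 analysed per arm. Assumed: each driver's crash rate varies around the mean with a gamma frailty of variance k. The article gives no value of k, so it is shown over a range.

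**Formulas.**
- Mean count μ, set so that the chance of at least one crash is 3%: μ = (0.97^(−k) − 1) / k.
- Variance divided by mean: 1 + kμ = 0.97^(−k).
- True SE divided by model-based SE, with both arms at the control rate: √(1 + kμ).
- True two-sided type I error: 2 × [1 − Φ(1.96 / √(1 + kμ))].

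For k = 2: μ = 0.0314, variance/mean = 1.063, SE ratio = 1.031, and type I error = 2 × [1 − Φ(1.901)] = 5.7%.

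| k (assumed) | μ | variance/mean | SE ratio | true type I error | coverage of 95% CI at 3% v 1.5% |
|---|---|---|---|---|---|
| 0.5 | 0.0307 | 1.015 | 1.008 | 5.2% | 94.9% |
| 1 | 0.0309 | 1.031 | 1.015 | 5.4% | 94.8% |
| 2 | 0.0314 | 1.063 | 1.031 | 5.7% | 94.5% |
| 5 | 0.0329 | 1.165 | 1.079 | 6.9% | 93.8% |
| 10 | 0.0356 | 1.356 | 1.165 | 9.2% | 92.4% |
| 20 | 0.0419 | 1.839 | 1.356 | 14.8% | 89.1% |

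The model-based SE is too small by 1 − 1/ratio: about 1% to 3% for k = 0.5 to 2, 7% at k = 5 and 14% at k = 10.

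The last column uses the variance of the log rate ratio with the two arms at their own rates. The mismatch is milder there because the intervention arm has fewer crashes.

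**What each k implies for repeat crashes.** Among 1,534 control drivers, about 46 crash at least once (0.03 × 1,534). With no heterogeneity, about 1.5% of these crash more than once, which is fewer than one driver. At k = 2 it is 4.5% (about 2 drivers), at k = 5 it is 8.6% (about 4), and at k = 10 it is 15% (about 7).

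**Simulation check.** 10,000 trials per value of k were simulated, with 1,534 per arm and mean 0.03 in both arms. This mean is slightly below the μ in the table, so the errors at high k are slightly lower.

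| k | type I error, model-based SE | type I error, robust SE |
|---|---|---|
| 0 | 4.6% | 4.5% |
| 1 | 4.7% | 4.5% |
| 2 | 5.7% | 5.0% |
| 5 | 7.0% | 5.2% |
| 10 | 8.2% | 5.1% |

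Robust errors stay close to 5% throughout and do no harm when there is no over-dispersion.

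**The case against.** The strongest reply is that the article does not say robust errors will be left out. It names a Poisson model and stops, and the variance estimator for one secondary model is the sort of detail that an analysis plan supplies. This stands as far as it goes: a reader might infer that the trial has chosen model-based errors, but that rests on silence. What remains is that the article does fix the model, and the model as stated carries no protection against over-dispersion.

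A reader might also see a contradiction, since robust errors are named for the other Poisson models. There is none. Those models fit a Poisson likelihood to yes/no outcomes, where its variance is known to be wrong and robust errors are the standard correction. For a true count, Poisson is a natural default.

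A third reply is that the distortion is negligible unless heterogeneity is extreme. This largely stands. For k up to 2 the type I error stays below 6%, and a material effect needs k of about 5 or more. The article has no repeat-crash figure to support such a value, and none to rule it out. It would therefore be wrong to state as fact that these counts are heavily over-dispersed or that the intervals will be seriously too narrow.

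**Conclusion.** The point holds as a minor improvement. As written, the crash-count analysis makes no allowance for differences in crash risk beyond state and sex, and model-based standard errors would be too small to the extent that such differences exist. The size depends wholly on the assumed frailty variance: true type I error is about 5.2% to 5.7% for moderate values (0.5 to 2), about 7% at 5 and about 9% at 10. These figures assume gamma frailty, 1,534 analysed drivers per arm and a crash risk of 3% in both arms.

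A reader might infer that the main result is at risk. It is not: the primary outcome is whether a driver crashed at all, is analysed by log-binomial regression, and has a fallback with robust errors. The sample size is also unaffected.

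**What to change.** Add one clause to the crash-count sentence under Secondary outcomes, or to the analysis plan: the Poisson regression for the total number of police-reported crashes will use robust (sandwich) standard errors. The estimated rate ratio, the covariates and the sample size stay as they are, and no further data are needed.

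Negative-binomial regression is not needed. At the planned risks about 69 drivers would crash at least once (1,534 × 0.03 + 1,534 × 0.015), few of them more than once, so its dispersion parameter would be poorly estimated.

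In the same edit, as a purely clerical matter, the crash count could be added to the secondary outcomes listed under Hypotheses and outcome measures, where it does not appear.
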